## Abstract

**Background:**

Intimate partner violence (IPV) victimization is a prevalent issue among women residing in Mexico City. Comprehensive and integrated health care provider (HCP) delivered programs in clinic-settings are needed, yet few have been evaluated in Latin America, including Mexico. In addition, there has been minimal attention to interventions among lower income women presenting at settings outside of antenatal care clinics. The current randomized controlled trial seeks to increase midlevel HCPs’ capacity, specifically nurses, who are often the first point of contact in this setting, to identify women presenting at health clinics with experiences of IPV and to assist these women with health risk mitigation. Specific outcomes include changes in past-year IPV (physical and/or sexual), reproductive coercion, safety planning, use of community resources, and quality of life.

**Methods/Design:**

Forty-two public health clinics in Mexico City were randomized to treatment or control clinics. Nurses meeting eligibility criteria in treatment groups received an intensive training on screening for IPV, providing supportive referrals, and assessing for health and safety risks. Nurses meeting eligibility criteria at control clinics received the standard of care which included a one-day training focused on sensitizing staff to IPV as a health issue and referral cards to give to women. Women were screened for eligibility (currently experiencing abuse in a heterosexual relationship, 18-44 years of age, non-pregnant or in first trimester) by research assistants in private areas of waiting rooms in health clinics. Consenting women completed a baseline survey and received the study protocol for that clinic. In treatment clinics, women received the nurse delivered session at baseline and received a follow-up counseling session after three months. Surveys are conducted at baseline, three months, and fifteen months from baseline.

**Discussion:**

This study will provide important insight into whether a nurse-delivered program can assist women currently experiencing abuse in a Latin American context. Findings can be used to inform IPV programs and policies in Mexico City’s public health clinics.

**Trial registration:**

NCT01661504

## Background

Intimate partner violence (IPV) against women is a critical health, human rights, and development concern, with global estimates indicating that approximately one in three women have reported such violence at some point in their life
[1]. Research has documented a range of negative health effects from IPV, including poor mental health, unwanted pregnancies, reproductive coercion, and vulnerabilities to HIV and sexually transmitted infections
[2–7]. Within Mexico, approximately 25%-40% of women who receive health sector services have reported violence from their partners at some point in their life
[8–10]. These lifetime IPV figures are comparable to other countries in Latin America and the Caribbean
[11], and underscore the importance of interventions in health care settings. These approaches are critical as women experiencing IPV have been shown to disproportionately utilize health care services
[12], and providers may be in a unique opportunity to intervene as they are among the few outside contacts a woman may have exposure to.

Despite the potential importance of health care provider (HCP)-delivered IPV interventions and in particular, HCP IPV screening programs, such approaches remain controversial
[13, 14]. Much of the debate surrounding the screening of women for IPV by HCPs is due to mixed evidence regarding the effectiveness of such approaches in reducing IPV and improving health outcomes
[15, 16]. Moreover, IPV screening by HCPs is not universally recommended by professional health organizations
[17]. However, it remains unclear if the screening alone is an ineffective approach for addressing IPV or if HCPs do not fully adhere to screening protocols. Lack of fidelity towards consistent screening has been noted in systematic reviews due to a variety of barriers perceived by HCPs
[18]. In addition, as studies evaluating screening for IPV involve vulnerable populations of abused women, there may be high levels of attrition
[15], which may vary differentially by severity of IPV victimization and thus limit extrapolation of findings. However, the evidence-base is growing to suggest that comprehensive and systems-approaches to identifying and counseling women experiencing IPV in health settings is an effective strategy
[19–21] to address both IPV victimization and related health concerns.

Thus, rigorous evaluations, including randomized controlled trials, of these combined and integrated HCP approaches are needed
[17]. In particular, there is limited evidence of their utility in Latin American countries, such as Mexico, including attention to the potential mitigation of broader health outcomes that are consistently associated with IPV, such as quality of life. One key health outcome that may also be reduced with integrated screening and counseling programs is reproductive coercion, which may involve birth control sabotage or other pressure to become pregnant
[22, 23]. In addition, while one pilot study conducted in Peru documented increases in safety planning behaviors among abused pregnant women who were screened for violence and received a counseling-based empowerment intervention, uncertainty exists regarding the effectiveness of safety planning or related counseling approaches in low and middle income countries in clinics that do not focus solely on antenatal care
[24]. The examination of such broader short and long-term health outcomes within the context of HCP delivered IPV interventions has been increasingly highlighted as an important area of intervention research
[16, 25].

Evaluations of the efficacy of these HCP responses to IPV are particularly needed within Mexico City, as the health system’s response to IPV has been fragmented at best. Briefly, Mexico City’s Ministry of Health (MoH) began implementing a domestic violence program in 2006. This program focused primarily on training health staff at hospitals on violence prevention and referral, in accordance with their internal protocol regarding IPV
[26]. The IPV program run by the MoH operates only within select hospitals (12 out of 31); the program has staff specifically assigned to offer psychological services to victims of IPV. However, despite interest in expansion and efforts by organizations in the region to build public sector capacity to address IPV, the program has not expanded due to limited resources
[27].

Additional challenges of the health sector response to IPV were noted in the planning phase of the study after in-depth discussions with the MoH and nurses at clinics. First, HCPs, hereafter nurses, at health clinics have limited to no information about where to refer IPV cases screened at the health clinics. Furthermore, nurses were given a self-efficacy test and knowledge test related to IPV as part of piloting the intervention and results showed that only 45% of nurses (n = 187) were prepared to make appropriate referrals for women experiencing IPV. Similar challenges regarding skills, referral systems and general knowledge of IPV have also been noted in other health sector responses in low and middle income countries
[28, 29]. In addition, despite efforts to address IPV
[30], there have been no trials in this context to assess effectiveness of health sector interventions in Mexico City. This is in contrast to the recent improvement in Mexican legislation which recognizes the right of women to live free from violence, and asks for improvements in the provision of services to the population
[31].

To address these gaps in knowledge, we are conducting the currently described randomized controlled trial to assess the efficacy of a comprehensive HCP delivered intervention in Mexico City. The primary objective of the study is to increase nurses’ capacity and self-efficacy to identify IPV and assist women with risk mitigation. Through this objective, nurses will be equipped to provide counseling and information for women experiencing IPV, linking women to resources in their community, creating safety plans to reduce risk of severe violence, and to mitigate any adverse health risks. The trial outcomes are to: (1) assess the efficacy of an enhanced nurse-delivered screening and counseling program on the primary outcome past year IPV, including severe IPV (sexual or physical) and injuries from such IPV
[32]; and secondary outcomes (b) reproductive coercion
[23] (c) use of community-based resources and safety planning
[33]; and (d) quality of life and mental health
[34]; versus minimum standard of care; (2) to qualitatively examine which programmatic components may serve as mechanisms for observed quantitative changes stated in the outcomes; and (3) to synthesize study findings and (a) create recommendations for clinic-based intervention programs to address IPV in low and middle income countries and (b) disseminate information as reports, presentation, and peer-reviewed publications.

## Methods/Design

### Study design

Our study utilizes a cluster-randomized controlled trial design and will take place between 2012 - 2015. Briefly, 42 public health clinics (first level of care facilities) were randomized to either the treatment or control conditions and women are to be assessed for information at baseline, time 2 (3 month follow-up), and time 3 (15 month follow-up). Further details are described below.

### Study setting

Mexico City, the capital and most populous urban center of Mexico, provides the study setting in which our research will occur. In this megacity, almost half of the population is uninsured (approximately 3,859,963 residents)
[35]. The uninsured population receives health care, through the federal health care program, Seguro Popular, at MoH clinics in Mexico City, this public insurance scheme aims at providing universal health care; a right recognized in the Mexican constitution of 1983
[36].

The MoH health system in Mexico City comprises 206 health clinics and 31 hospitals. The 206 MoH clinics are classified into Type I, Type II and Type III based on level of care. Clinics classified as Type III are large clinics that offer a broader array of services than Type I or II clinics. For instance Type III clinics offer laboratory tests. Clinics classified as Type I and II, are community clinics with 1 or 2 doctors and about 2 nurses; their focus is on community outreach and immunizations with Type I being the smallest level of community health center. Type III clinics were selected to participate in the study after conversations with the MoH because of their lack of IPV services and larger patient volume compared to Type I and Type II. These Type III clinics, chiefly located in low and middle income neighborhoods, serve primarily a low income population, and are thus eligible for the Seguro Popular. The number of women served by these health clinics varies greatly from borough to borough. Over 2,336,000 residents use the services of the MoH health clinics and hospitals annually
[37].

At these Type III primary care clinics, the first points of contact for patients are nurses. The flow of patients at these clinics is as follows: patients line up early in the morning in order to get an appointment on a first come first served basis; although the MoH is currently implementing an appointment system that will reduce waiting times for patients. Nurses take somatometry measurements on all patients before they are seen by the doctors. Social workers do not have contact with every patient unless they are specifically needed in instances if patients need a referral to a hospital or to a different health clinic.

Out of the 60 Type III health clinics, one was excluded from potential recruitment because it was located in the borough of Milpa Alta; a remote and rural location with limited access to community resources and a small populace (<2% of Mexico City’s population). Two additional clinics were excluded to reduce contamination. These hospitals were located less than three blocks from hospitals and some hospitals also had violence against women programs.

### Randomization, sample size, and power analysis

Approximately 900 women from 42 health clinics were calculated to be sufficient sample size in order to achieve 80% power to detect a 15% difference in IPV frequency between treatment versus control arms at the α < 0.05 statistical significance level. A conservative intraclass correlation of 0.07 was assumed for clustering at the clinic level. This total sample size takes into account an attrition rate of 45%. The study proposal has budgeted for tracking participants that are relatively more difficult to track in order to reduce attrition.

Health clinics were first stratified by city zone (e.g. Center, North, East, West, South). Of the 57 health clinics that met inclusion criteria, 42 were randomly selected and randomized to treatment or control conditions, based on sample size calculations. To select the 42 health centers, all centers were assigned random numbers in Excel and sorted from smallest to largest; health centers were selected based on city zone and in order of their random number. Randomization was completed in STATA.

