### Quantitative assessments & analytic plan

Our primary outcome is past-year IPV
[32] and our secondary outcomes include past-year reproductive coercion
[7, 23], use of community-based resources
[33], safety planning measures
[33], and quality of life
[34]. Descriptive statistics will be used to assess achievement of Aim 1. For the remaining aims, the follow analyses plans will be undertaken: (1) assess if randomization of health clinics was successful by examining if there are statistically significant differences between women’s demographics, by treatment arm, through chi-square or t-tests; (2) assess for differential loss to follow up by demographics and baseline IPV severity; (3) assess if IPV and secondary outcomes (reproductive coercion, safety planning, use of community resources, quality of life) differed at baseline, by treatment arm; and (4) conduct multilevel analyses of the effect of the intervention on outcomes utilizing appropriate models that will account for potential clustering for repeat measures, time, and at the clinic level. We will subsequently estimate adjusted models if any demographics significantly varied at baseline. Analyses will first be undertaken using the intent-to-treat approach. Following this, a per protocol analysis will be undertaken to determine whether effectiveness varied by adherence (i.e. attending the three month booster counseling session) and potentially nurse adherence.

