## Discussion

This study seeks to train and improve nurses’ capacities to deliver an intervention for women currently experiencing IPV that present at health clinics in Mexico City. If found efficacious, this study may have an important influence on programming and policy for the health sector responses in city-based clinics serving low-income women in the region. Findings may also contribute to the evidence-base for comprehensive prevention strategies to reduce IPV and to respond to the needs of survivors. This intervention may be an effective health-sector tool to reduce IPV and mitigate negative effects, in addition to many other approaches including changes in the legal system or other social change approaches that focus on gender equality and the engagement of men to reduce violence
[47–49].

Despite the strong study design to assess the efficacy of the HCP delivered intervention on outcomes, limitations and potential problems have been considered. As with other randomized controlled trials, participant drop-out and differential attrition is a concern
[19]. To address potential problems, we have added an exclusionary criterion that women do not plan on relocating within the study period. At the time of enrollment, we also verify contact information for the woman and obtain information for three additional contacts that would know how to get in touch with her. In the analysis plan, we will assess for differential attrition and potentially adjust final models for variables that may have statistically differed between treatment arms. Other approaches may also be used to handle missing data, including multiple imputation, which has been used in other studies examining IPV screening effectiveness
[15].

In addition, staff at referral community agencies that are aware of and engaged with the study may also turnover, which may have a bearing on the quality of service provision. As noted in literature regarding health sector responses to IPV, linkages to community agencies may be a critical component of success

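### The stated covariate rule is triggered by significance tests on demographics; city zone and baseline IPV severity should be prespecified in the primary model instead

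*Protocol article*

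**What the plan says.** All places are in the Protocol article.

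- **Model.** Quantitative assessments & analytic plan calls for "appropriate models that will account for potential clustering for repeat measures, time, and at the clinic level". No covariate is named with it.
- **Adjustment rule.** The same section continues: "We will subsequently estimate adjusted models if any demographics significantly varied at baseline". In the Discussion, in the context of attrition, the authors would "potentially adjust final models for variables that may have statistically differed between treatment arms".
- **City zone.** Randomization, sample size, and power analysis states: "Health clinics were first stratified by city zone (e.g. Center, North, East, West, South". It then says that "health centers were selected based on city zone and in order of their random number". Allocation to arm is described only as having been done in STATA; whether it was done within zone is not stated.
- **Baseline IPV.** The analytic plan gives it two uses. One is to "assess for differential loss to follow up by demographics and baseline IPV severity". The other is to "assess if IPV and secondary outcomes (reproductive coercion, safety planning, use of community resources, quality of life) differed at baseline, by treatment arm". Neither is linked to an adjustment in the primary model.
- **Eligibility.** Study population, recruitment, and retention requires a positive answer on past-year physical or sexual IPV.

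**The concern.** The rule chooses covariates by whether a test happens to be significant, not by whether they predict the outcome or belong to the design. It has two weaknesses. It can fire by chance on a demographic that does not matter. And because the analytic plan's version covers demographics only, it stays silent on zone and IPV severity, whatever their imbalance.

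For zone, the consequence depends on how clinics were allocated. If allocation was within zone, leaving zone out keeps zone differences in the between-clinic error, so the test is conservative and some precision is lost. If zone governed only the choice of 42 from 57 clinics, a chance imbalance in zone between arms goes unadjusted.

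For baseline IPV, if the primary outcome is analysed as yes/no, the baseline value is nearly constant because of eligibility and carries little information. Severity or frequency does vary. With 42 clinics, and research assistants who knew the clinic's arm when they recruited, the arms could differ in severity by chance or by selection.

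**Working it through.** **Inputs from the article:** about 900 women, 42 clinics, ICC 0.07, attrition 45%, 15% difference, 80% power, alpha 0.05.

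**Assumed here, because the article does not give them:** control rate; an absolute 15-point difference; a two-sided test; equal arms; five zones (the article lists five as examples); the share *z* of between-clinic variance explained by zone; the correlation *r* of baseline severity with outcome.

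**1. The plan's own figure.** Retained women: 900 × 0.55 = 495, or 495/42 = 11.79 per clinic. Design effect: 1 + 10.79 × 0.07 = 1.755. Effective number per arm: 247.5/1.755 = 141. Power for a 15-point difference (null variance pooled) is:

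- 57.5 vs 42.5%: 71.4%
- 70 vs 55%: 74.2%
- 80 vs 65%: 80.9%
- 90 vs 75%: 91.7%

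At 80 vs 65% the required number is 881, close to 900. So the stated size is attainable at a control rate near 80%, but without the base rate it cannot be confirmed.

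**2. Gain from adjustment, analytic.** Relative variance of the arm difference, on the linear scale:

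[ICC(1 − z) + (1 − ICC)(1 − r²)/m] / [ICC + (1 − ICC)/m], with m = 11.79.

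The denominator is 0.07 + 0.93/11.79 = 0.1489. Power below is for 50 vs 35% (unpooled variance). The unadjusted standard error is √[(0.25 + 0.2275)/141] = 0.0582, so 0.15/0.0582 − 1.96 = 0.62, or 73.2%.

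| z | r | Relative variance | Power | Gain (points) |
|---|---|---|---|---|
| 0 | 0 | 1.000 | 73.2% | – |
| 0.2 | 0 | 0.906 | 77.3% | 4.1 |
| 0.4 | 0 | 0.812 | 81.6% | 8.4 |
| 0.2 | 0.4 | 0.821 | 81.2% | 8.0 |
| 0.4 | 0.4 | 0.727 | 85.6% | 12.4 |

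At other rates, with zone share and within-clinic R² both 0.2 (relative variance 0.800), power moves from 71.4 to 80.7% at 57.5 vs 42.5%, and from 80.9 to 88.7% at 80 vs 65%.

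**3. Gain from zone, by simulation.** The formula above ignores the degrees of freedom spent on zone. A simulation of clinic means (8,000 runs per cell, five zones, allocation assumed within zone, 57.5 vs 42.5%) includes them:

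| Zone share | Power without zone | Power with zone | Type I error without zone | Type I error with zone |
|---|---|---|---|---|
| 0 | 70.2% | 69.8% | 4.7% | 4.8% |
| 0.2 | 71.2% | 74.4% | 3.8% | 4.9% |
| 0.4 | 71.2% | 78.5% | 2.8% | 4.9% |

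Zone alone therefore adds nothing at a zero share, and about 3 or 7 points at 20 or 40%. The error rate without zone falls below 5%; it does not rise above it. Adding a baseline score with R² 0.2 takes power with zone to 78.8 and 84.1% at the last two shares.

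**4. How often the stated rule fires by chance.** With *k* independent demographics tested at 5%, the chance of at least one significant result is 1 − 0.95^k: 23% for 5, 34% for 8, 40% for 10. The number of demographics is assumed.

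**The case against.** The strongest reply is that the article gives no model equation. The terms it lists describe the correlation structure, and a covariate list is commonly left to a fuller document that is not shown. That stands: zone and severity are not named, which is different from being excluded. It does not answer the point, because the adjustment rule is stated, and a later plan could improve on it only by replacing it.

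A reader might also infer several stronger things that the article does not support:

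- **That standard errors are certainly too large for a stratified design.** The text ties zone clearly to clinic selection, not clearly to allocation.
- **That baseline IPV serves only the attrition check, and that nothing beyond demographics could be adjusted for.** Baseline IPV is also compared by arm, and the Discussion allows wider adjustment at discretion.
- **That baseline IPV cannot already be in the model.** Baseline is one of three surveys in a repeated-measures analysis. If the outcome is a score or frequency, its baseline value may enter as a measurement. The sample size text speaks of IPV frequency, so a yes/no outcome is one reading only. The eligibility screen and the outcome measure also cite different sources, so a yes/no baseline is nearly constant, not necessarily exactly so.
- **That the trial falls short of 80% power without adjustment.** Unadjusted power runs from 71.4 to 91.7% over the control rates tried.

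Two technical limits also stand. The variance formula is linear and does not carry over directly to the log odds ratio of a logistic mixed model. And adjusting for one severity score would not fully remove selection from unblinded recruitment.

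**Conclusion.** The point holds in a limited form. The adjustment rule in the analytic plan depends on significance tests of demographics, the Discussion adds only a discretionary variant, and neither commits the trial to adjusting for city zone or baseline IPV severity. It is a poorly chosen rule that can be improved with data already held; it does not make the analysis invalid. The benefit ranges from none, if neither variable is prognostic, through about 3 to 7 power points for zone alone at a 20 to 40% share, to roughly 8 to 12 points if severity is prognostic too. The base rate, zone share and severity–outcome correlation behind these figures are all assumptions. If allocation was within zone, omitting it errs on the conservative side; if not, adjustment corrects chance zone imbalance. Including zone is reasonable under either reading.

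**What to change.** Replace the significance-triggered rule with a fixed covariate set:

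- Primary multilevel model: arm, city zone as a fixed effect, baseline IPV severity or frequency, and a clinic random effect, alongside the planned terms for time and repeated measures, whatever the balance tests show.
- Secondary outcomes: each outcome's own baseline value, either as a covariate or through a repeated-measures model that constrains the arms to a common baseline mean.
- Report the unadjusted model as a sensitivity analysis, and keep the baseline comparisons as description only.
- State whether clinics were allocated to arm within zone.

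The cost is wording in the analysis plan and, with five zones, about 4 cluster-level degrees of freedom (42 − 2 = 40 without zone, 36 with it). No new data are needed. At resubmission of the article only the baseline and three-month surveys were complete, so on that status the set could still be fixed before the fifteen-month analysis.
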